## Abstract

**Background::**

Traumatic brain edema occurs commonly brain injury, and most manifests as pericontusional edema of brain contusions. On the basis of evidence-based medicine, apart from recommending craniotomy and mannitol, there are few particularly effective measures to prevent and treat traumatic brain edema. It is uncertain whether an early complementary acupuncture treatment would improve long-term outcomes of patients with traumatic brain edema. The aim of this study is to assess the efficacy and the safety of early complementary acupuncture for patients with traumatic brain edema.

**Methods::**

This study is an actively accruing, single-center, single-blinded, 2-arm, randomized controlled trial. Patients with traumatic brain injury, a Glasgow Coma Scale score of 6∼12, and brain edema on computed tomography scan will be divided into 2 groups on the basis of stratified block randomization. All patients will receive conventional treatment, and the study group will undergo additional acupuncture therapy (start within 72 hours after the injury) once a day for 28 days. The primary outcome is the dichotomized Glasgow Outcome Score at 6 months and 12 months after injury, and the secondary outcomes are the Glasgow Coma Scale, the volume of traumatic brain edema, the serum levels of C-reactive protein and interleukin-6, and the Modified Barthel Index.

**Discussion::**

This study will provide data regarding the efficacy of early complementary acupuncture for traumatic brain edema. If the study yields positive results, its findings may offer insights into a valuable complementary option of acupuncture for traumatic brain edema that could provide pilot evidence for large, randomized, controlled trials.

**Trial registration:** This trial has been published in the Chinese Clinical Trial Register, http://www.chictr.org.cn/edit.aspx?pid=141208&htm=4 (Identifier: ChiCTR2100053794, registered on December 3, 2021).

## Introduction

1

Traumatic brain edema (TBE) is defined as a pathological condition in which the fluid content in the brain tissue increases abnormally and the brain volume increases after traumatic brain injury (TBI) or craniotomy; TBE commonly manifests as pericontusional edema after brain contusions.^[1]^ Localized cerebral edema, erupting simultaneously with brain contusions, might lead to increased intracranial pressure (ICP), cerebral herniation, and ultimately death.^[2]^ TBE, an independent prognostic variable of all severe TBI, is the most common and serious complication of TBI. TBE contributes to approximately 50% of the deaths of patients with severe TBI.^[3]^ In China, 53.17% of patients experience unfavorable outcomes from TBI, which include severe disability, a vegetative state, and death.^[4]^ As medicine has advanced rapidly, the survival of patients with TBI has also improved in recent years. However, the long-term treatments needed for the survivor place inconveniences and financial pressures on the family and society.^[5]^

TBE is a major cause of death and severe, prolonged disability in patients with TBI. Research on the treatment and the prevention of TBE has continued for more than half a century, but there has been no breakthrough in this field. Evidence from evidence-based medicine have shown that only few other treatments have definite efficacy for TBE beyond craniotomy and mannitol.^[6]^ However, craniotomy and mannitol treatment have limitations. For example, brain edema may progress after craniotomy, and mannitol may cause adverse effects that include ICP rebound and kidney damage.^[7]^

Although effective therapeutic approaches for TBE remain limited, researchers continue to make meaningful attempts to determine effective and alternative treatment options, such as acupuncture for TBE. For patients who are unconscious after TBI, acupuncture may improve the Glasgow Coma Scale (GCS) score^[8,9]^; increase wake-promoting rates (Wake-promoting rates refers to the percentage of patients who recovered to GCS 15 to the total number of patients in this group at the end of treatment.)^[10,11]^; and change the GOS grade,^[12]^ which improves the prognosis. However, studies conducted previously by our team have demonstrated the fact that acupuncture could promote the absorption of traumatic intracerebral hematoma and brain contusion lesions, and improve the quality of life of such patients.^[13,14]^ Even though the acupuncture has been observed to be an effective treatment for patients with TBI, some of the acupuncture data remain weak and unconvincing.^[15]^ Few studies have investigated acupuncture as an adjuvant therapy in the acute phase of TBI (within 2 weeks after injury), which high-quality randomized controlled trials (RCTs) are particularly lacking.^[16]^ For this reason, and taking into account the preliminary results of the previous trials, a standardized RCT is planned to assess the effect of acupuncture on the prognosis of patients with TBE. The method of monitoring and quantitatively analyzing brain edema based on head computed tomography (CT) can be very convincing, and complementary acupuncture treatment in the acute-phase TBI (starting within 72 hours after injury) can be a novel idea of designing in this clinical trial.

If TBE is not controlled, the ICP will continue to increase, which can lead to fatal brain herniation.^[6]^ This unfavorable prognosis of TBE emphasizes the importance of managing the increased ICP in patients with TBE. Although the technology of ICP monitoring is precise and accurate, its invasive operation possibly harms patients.^[17]^ As a noninvasive examination for TBI, CT scans play a vital role in the study of brain edema; the CT images can evaluate ICP at an acute phase TBI, and software is used to reduce the subjectiveness of quantifying brain edema.^[18,19]^

The pathological mechanism of TBE is unclear. After injury, the neuroinflammatory cascade that is considered an important mechanism of TBE promotes the rapid progression and progressive aggravation of TBE.^[20]^ Highly expressed inflammatory factors in the damaged brain tissue [e.g., C-reactive protein (CRP) and interleukin-6 (IL-6)] are released into the blood circulation; then, the degree of nerve tissue damage and the prognosis can be judged according to the serum levels of inflammatory factors.^[21]^ Many clinical studies have provided evidence of the anti-inflammatory effects of acupuncture. For example, Chen et al^[22]^ have concluded that acupuncture could downregulate the levels of inflammatory factors (IL-6 and IL-8) in patients with TBI, whereas Cho et al^[23]^ have found that acupuncture could reduce CRP levels in patients after craniotomy.

TBE is a complex and changeable pathological process, and the appropriate target cohort of treatment should be selected in order to measure the effectiveness of acupuncture. Here, we present the study protocol for a RCT to examine whether complementary acupuncture on acute-phase TBI is effective compared against the conventional treatment alone in patients with TBE. In addition, the study will also observe whether acupuncture is associated with an anti-inflammatory effect and a reduction in the volume of brain edema.

We present the following article in accordance with the SPIRIT reporting checklist.

## Methods/design

2

### Trial design and setting

2.1

This study is a single-center, outcome-assessor, and statistician-blinded, randomized, and controlled trial that was devised according to the Standards for Reporting Interventions in Clinical Trials of Acupuncture.^[24]^ The study consists of 4 stages: enrollment, allocation, intervention, and analysis. Each participant will be registered only once. The total study period for this trial will be 12 months (follow-up to 12 months after injury), including a 1-month treatment phase. This is the initial version of the protocol. The start of this study will been plan on January 10, 2022, and ends on June 10, 2024. It may be completed ahead of schedule if a sufficient number of patients are recruited.

The study will be carried out in the Neurosurgery Center of Qionghai People's Hospital, Hainan Province, China, and all participants will be recruited from the inpatients in this center. A minimum of 40 patients who meet the eligibility criteria and sign an informed consent form are expected in this hospital each year. Patients with TBI (GCS score of 6∼12 and brain edema on CT scan) will be divided into 2 groups; the control group will receive conventional treatment, and the study group will receive additional acupuncture as an adjuvant therapy, once a day for 28 days, starting within 72 hours after the injury.

### Recruitment strategies

2.2

Inpatients at the Neurosurgery Center of Qionghai People's Hospital, Hainan Province, China, will be recruited in this RCT. Patients with a GCS score of 12 or lower would not be capable of giving informed consent to participate in a clinical trial, so all relatives (or legal representatives) of patients will be able to consent to participate or drop out at any time. The responsible doctor will briefly explain to the relatives that the patient will receive the usual treatments for TBE but that, in addition to these, the patient in the study group will also undergo acupuncture as an adjuvant therapy. The benefits and possible risks of the trial will be described, and patient representatives will be required to sign the informed consent before the trial begins. The flowchart of enrollment, allocation, interventions, and analysis is presented in Figure 1.

**Figure 1 F1:**
[figure not shown]
Flowchart of enrollment, allocation, interventions, and analysis in the trial. CRP = C-reactive protein, GCS = Glasgow Coma scale, GOS = Glasgow outcome score, IL-6 = interleukin-6, MBI = Modified Barthel Index, TBE = Traumatic brain edema. ^*^Wake-promoting rates refers to the percentage of patients who recovered to GCS 15 to the total number of patients in this group at the end of 28 days of treatment.

### Participants

2.3

#### Eligibility criteria: inclusion criteria

2.3.1

Adults with TBI who fulfill the following inclusion criteria are eligible: an initial GCS score between 6 and 12 on admission; one or more brain contusions with visible pericontusional edema on the CT scan; age between 16 and 75 years; agreement to undergo acupuncture treatment within 72 hours after injury or craniotomy; and completion of informed consent by a legal representative.

#### Eligibility criteria: exclusion criteria

2.3.2

The exclusion criteria are as follows: unstable vital signs within 72 hours of admission; a concomitant, severe medical disease (e.g., heart, liver, renal failure, or an autoimmune disorder); craniotomy before random assignment for any reason other than TBI; unsuitability for acupuncture (e.g., pregnant, diagnosed with frequent seizures or psychotic disorders, fear of acupuncture, particularly weak, skin infections at the acupuncture site); and need for medication to treat coexisting diseases that may affect the results of the study.

### Randomization and blinding

2.4

To ensure a balanced sample size across groups over time, the study is using stratified block randomization in a 1:1 ratio that divides patients into 2 groups according to the GCS (scores of 6∼8 or 9∼12). The study will also apply block randomization method with a block size of 2 (post-craniotomy or no craniotomy).

Random numbers will be made by a computerized number generator list provided by a statistician not involved in the determination of eligibility or in the assessment of outcomes. The allocation of participants will be sealed in sequentially numbered, opaque envelopes.

After verification that a patient meets all the inclusion criteria and none of the exclusion criteria, and after the informed consent is signed by legal representative, the doctor responsible for the patient will assign a correlative number to the patient who will be allocated to either the study group or the control group.

The blinding of this study is limited because it is easily discernible that some patients are receiving acupuncture therapy, and the acupuncturist cannot be blinded. However, the outcome assessors and statistician will be blinded and unaware of patient allocation. During the whole research process, unblinding will be carried out after the statistical analysis is completed.

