The treatment plans for patients with TBE and the measurement of treatment effect are usually based on evaluating the ICP level at an acute-phase TBI. The ICP measure is commonly estimated by clinical judgment according to neurofunctional evaluation and CT image interpretation.^[18,35]^

This feasibility trial has the necessary optimizing features that may be helpful for future trial designs in TBE. However, some limitations still exist in this study. First, the number of cases is relatively small and is collected from a single center, which may have led to overfitting of the protocol. Second, we are adopting a single-blinding approach; because of the characteristics of acupuncture, the therapists and the participants cannot be blinded in this study. Finally, limiting participation of patients of age 16 to 75 years and with GCS scores of 6 to 12 means that the study results cannot be applied to all patients with TBI.

In conclusion, this pragmatic study protocol will allow us to determine the actual effects of acupuncture during real-life conditions in normal medical practice for TBI. Positive results from our study may lead to insights about a valuable complementary acupuncture option for TBE and could provide pilot evidence for additional and larger RCTs. This study has the potential to change recommendations for acute-phase acupuncture as a treatment for patients with moderate to severe TBI.

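### Read literally, fixed blocks of 2 within strata let the second allocation of each pair be deduced in this open, single-centre trial; the sentence may instead mislabel a stratification factor

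*Protocol article*

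**What the plan says.** All references are to the protocol article.

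- **Stratification (2.4 Randomization and blinding).** "the study is using stratified block randomization in a 1:1 ratio that divides patients into 2 groups according to the GCS (scores of 6∼8 or" 9 to 12).
- **Block size (2.4).** The next sentence reads "The study will also apply block randomization method with a block size of 2 (post-craniotomy or no craniotomy").
- **Concealment (2.4).** An independent statistician supplies the list. "The allocation of participants will be sealed in sequentially numbered, opaque envelopes".
- **Who allocates (2.4).** After eligibility has been verified and consent signed, "the doctor responsible for the patient will assign a correlative number to the patient". The text does not say who verifies eligibility.
- **Who approaches the family (2.2 Recruitment strategies).** "The responsible doctor will briefly explain to the relatives that the patient will receive the usual treatments for TBE", and that the study group also has acupuncture.
- **Visibility (2.4 and Discussion).** "it is easily discernible that some patients are receiving acupuncture therapy, and the acupuncturist cannot be blinded"; the Discussion adds that "the therapists and the participants cannot be blinded in this study". Only the outcome assessors and the statistician are blinded.
- **Setting and training (2.1, 2.11).** There is one centre, which expects at least 40 eligible, consenting patients a year. All researchers are trained to understand the protocol fully, and the protocol contains the block size.

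The article nowhere says that the block size varies or is kept from recruiting staff.

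**The concern.** In a 1:1 block of two, the first allocation fixes the second. Sealed envelopes conceal an allocation only as long as it cannot be worked out from earlier ones. Here the earlier ones can be seen, because daily acupuncture over 28 days is evident to ward staff.

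Knowledge of the next arm could act at two points. One is the consent conversation, which the responsible doctor leads. The other is the exclusion list in 2.3.2, several items of which need judgement: whether a patient is too frail for acupuncture, whether vital signs are stable, and whether other medication might influence the results. If patients with a better outlook were entered more readily when acupuncture was due, or held back when control was due, the arms would differ at baseline. The primary comparison of good recovery on the GOS would carry that difference. Blinding the assessors and the statistician does not address selection at entry.

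**Working it through.** **Inputs.** Ratio 1:1, block size 2, GCS strata 6–8 and 9–12, possibly a craniotomy factor (2.4); N = 80 and planned good-recovery rates of 80% and 50% (2.9); at least 40 patients a year (2.1). The plan gives no figure for predictability, so there is none to reproduce. The sample size matters here only as the number of allocations.

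**1. Predictability of fixed 1:1 blocks of size 2b.**

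- Expected share of allocations fully determined by earlier ones: 1/(b + 1).
- Expected correct guesses per block, always guessing the arm used less so far: b + (4^b / C(2b, b) − 1)/2; divide by 2b for the rate.
- For b = 1: share determined = 1/2. Correct guesses = 1 + (4/2 − 1)/2 = 1.5 of 2, or 75%.

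| Fixed block size | Determined | Guessed correctly |
|---|---|---|
| 2 | 50.0% | 75.0% |
| 4 | 33.3% | 70.8% |
| 6 | 25.0% | 68.3% |

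Enumeration of all possible blocks gives the same values. Simple randomization would give a 50% guess rate.

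**2. Number determined among 80.** With blocks of 2, a stratum of n patients has floor(n/2) determined allocations. Simulation with equally likely strata (an assumption) gives:

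- one list: 40;
- two strata: 39 to 40;
- four strata: 38 to 40, mean 39.0.

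**3. Is tracking feasible?** At 40 patients a year the average gap is 365/40, about 9 days, and longer within a stratum. The previous patient's arm would usually be apparent before the next patient in that stratum is considered. Two to four running tallies are enough.

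**4. Randomly mixed blocks of 4 and 6.** Guessing the under-represented arm needs no knowledge of block size. By simulation:

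| Scheme | 20 patients in a stratum | 80 on one list |
|---|---|---|
| Fixed 6 | 67.0% | 68.0% |
| Mixed 4 and 6 | 68.5% | 69.2% |

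The fixed-6 rates fall just below 68.3% because 20 and 80 are not multiples of 6.

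**5. What selection could do (illustration; d is assumed, not taken from the article).** Half of each arm is determined. Suppose determined patients in the acupuncture arm have a d-point higher chance of good recovery, and those in control a d-point lower chance. The arm rates then move by +d/2 and −d/2, so the difference is biased by d. For d of 5 to 10 points, the bias is 5 to 10 points against a planned difference of 80 − 50 = 30 points.

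**The case against.** **The figure 2 may not be a block size.** The parenthesis lists the two levels of a craniotomy factor. If 2 counts those levels, no block size is stated and the 50% and 75% have no basis. This stands: the figures are conditional on the literal reading. It does not clear the sentence, which would then call a stratification factor a block size.

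**Predictability is local.** A reader might infer that every second allocation in the trial is known in advance. It is known only within a stratum, and only to someone who knows the last allocation there. That is feasible here, but not automatic.

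**Opportunity is not occurrence.** A reader might also infer that concealment has failed and the GOS result will be biased. The article supports neither claim; it shows only that the means are present.

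**Control of eligibility is not stated.** It is tempting to say that the responsible doctor decides eligibility. The text puts verification in the passive. Only explaining the trial and assigning the number are given to that doctor, so influence at consent is documented and influence over exclusions is inferred.

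**Analysis is not powerless.** Adjusting for measured baseline prognosis can reduce such bias. It cannot reach the unmeasured part.

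The independent list, the envelopes and the blinded assessors are sound features, but none of them hides an allocation that can be deduced. Nor is this a detail left to a fuller document, since the article states the block size itself.

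**Conclusion.** The point holds in conditional form. If 2 is the block size, about half of the allocations (about 39 to 40 of 80) are determined for anyone tracking the stratum, and 75% can be guessed. This rests on visible treatment, one centre, and a size that is neither varied nor withheld. The consequence is a possible, unquantified bias in the primary comparison that baseline adjustment can only partly remove. If 2 is the number of craniotomy levels, the defect is one of wording: the block size is unstated and the second stratification factor is mislabelled. Either way, the sentence should be corrected before further patients are randomised.

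**What to change.** Confirm what 2 means, then replace the two sentences on stratification and blocks with:

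*Randomisation is stratified by GCS (6–8, 9–12) and craniotomy (yes, no), using permuted blocks of randomly varying size; the sizes are known only to the statistician who generates the list and are withheld from recruiting staff.*

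Prepare one envelope series for each of the four strata. Print no sizes in the protocol, not even as an example.

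**Gain.** The end of a block can no longer be read off a known size, so most of the certainty goes. The best-guess rate falls only modestly, from 75% to about 68–69% for a mix of 4 and 6. Mixing does not beat fixed blocks of 6 on guess rate; its advantage is that block ends are hidden.

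**Cost.** A regenerated list and new envelopes; the sample size is unchanged. With blocks up to 6 the arms can differ by up to 3 within a stratum. The worst case is 4 × 3 = 12 over four strata, against 4 × 1 = 4 with blocks of 2; such an extreme is unlikely. The abstract describes the trial as already accruing, so the change applies to patients not yet randomised and cannot protect those already allocated.

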### Interventions

2.5

#### Interventions

2.5.1

In addition to conventional treatment, patients in the study group will receive acupuncture as adjuvant therapy, which will start within 72 hours after injury or craniotomy; acupuncture will be administered once a day for 28days (a total of 24 treatments with 1 break per week). All interventions will be performed by the same acupuncturist doctor, who has more than 10 years of clinical experience and who will be trained in the study protocol before the start of the trial. Encouragement and supervision from acupuncturists can help improve participants’ adherence.

Only sterile, stainless, disposable acupuncture needles (size: from 0.25 × 30 mm to 0.25 × 50 mm; Suzhou Hwato Acupuncture Medical Appliance Company, China; product no. 20162270970) will be used. In the study group, acupuncture needles will be inserted into acupuncture points located on the midline of the human body (GV20, GV26, and CV9) and on the affected limbs (GB20, GB39, PC6, LI4, ST36, ST40, SP6, KI7, and LR3). If the GV20 point is too close to the surgical site, this acupoint may be skipped. All the acupoints have been selected and localized according to the guideline of WHO Standardized Acupuncture Point Location, and then depending on where the needle is located the insertion depth will be 10 to 40 mm.^[25]^ The needles will be manipulated using twirling, lifting, and thrusting methods to promote Qi. Because patients are not able to express their feelings, eye moisture or the presence of tears will be considered as a kind of Deqi. After insertion, needles will be left in position for 30 minutes in every session and the manipulations of twirling, lifting, and thrusting will be repeated for 1 minute/10 minutes. The location of the relevant acupoints is summarized in Table 1.

**Table 1 T1:** Description of the location of the applied acupoints.

Acupoints	Descriptions
Baihui (GV20)	Straight up 5 cun above the middle of the front hairline
Shuigou (GV26)	At the junction of the upper and middle third of the philtrum
Fengchi (GB20)	Below the occiput, the depression between the upper end of the trapezius muscle and the upper end of the sternocleidomastoid muscle.
Xuanzhong (GB39)	On the outside of the calf, 3 cun above the tip of the lateral malleolus, and the depression of the front edge of the fibula
Shuifen (CV9)	On the upper abdomen, anterior midline, 1 cun above the middle of the umbilicus
Neiguan (PC6)	2 cun above the transverse crease of the wrist, between the palmar longus tendon and the flexor carpi radialis tendon
Hegu (LI4)	On the back of the hand, at the midpoint of the radial side of the second metacarpal bone
Zusanli (ST36)	3 cun down of the depression on the lateral side of the knee and 1 cun away of the front edge of the tibia
Fenglong (ST40)	On the anterolateral side of the calf, 8 cun above the tip of the lateral malleolus, the outer edge of the tibial anterior muscle
Sanyinjiao (SP6)	3 cun above the tip of the medial malleolus, posterior tibia
Fuliu (KI7)	2 cun above the tip of the medial malleolus, the front edge of the Achilles tendon
Taichong (LR3)	In the back of the foot, between the first and second metatarsals, in the anterior depression of the metatarsal junction

The “cun” in acupuncture is the bone-length proportion, which is divided by the body surface mark of the patient him or herself.

